**Enrollment**								
Eligibility screen	X							
Informed consent	X							
Allocation		X						
**Interventions**								
Chopsticks technique				X				
Cross technique				X				
**Assessments**								
Baseline characteristics			X					
Total operation time^a^				X				
Single-port establishment time^b^				X				X
Pelvic-abdominal adhesion release time^c^				X				X
Total hysterectomy time^d^				X				X
Specimen removal time^e^				X				X
Stump suture time^f^				X				X
Conversion to another LESS technique				X				X
Conversion to traditional laparoscopy /laparotomy				X				
Estimated blood loss^f^				X	X			X
Intraoperative complications				X	X			X
Surgeon fatigue (FSS)^h^					X			X
Post-operative hospital stay						X		X
Hospitalization expenses						X		X
Post-operative hospital stay						X		
Postoperative complications^i^							X	X
Health-related quality of life (EQ-5D)			X				X	X

^a^ Total operation time: the time from the beginning of the skin incision to the end of the operation

^b^ Single-port establishment time: the time from the beginning of the skin incision to the establishment of pneumoperitoneum

^c^ Pelvic-abdominal adhesion release time: the time taken to separate adhesions

^d^ Total hysterectomy time: the time from accessory/fallopian tube resection to uterine disconnection

^e^ Specimen removal time: the time taken to remove the uterus through vaginal or umbilical fragmentation

^f^ Stump suture time: the time taken for vaginal stump suturing with a single needle barb

^g^ Estimated blood loss: collected and evaluated by the intraoperative suction device

^h^ Fatigue Severity Scale (FSS): score on a 7-point scale (1 = strongly disagree, 7 = strongly agree), where a higher mean value manifests a higher degree of severity of fatigue symptoms [16]

^i^ Postoperative infection: lower abdominal pain with fever>38°C

We will not involve participant biological samples.

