No comparative studies have been conducted to compare different surgical efficiencies between LESS techniques thus far. Therefore, this study intends to verify the value of the “chopstick technique” in LESS-TH by comparing surgical efficacy and surgeon fatigue.

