### Interventions

Preoperative preparation

Patients will receive preoperative prophylactic antibiotics and will be given general anesthesia. A uterine manipulator will be placed.2.Surgeon

All the surgeons participating in the study are proficient in the two LESS techniques (“chopstick technique” and “cross technique”) and have completed more than 40 operations using both surgical methods [13], which cumulatively exceeds the learning curve turning point.3.Surgical treatmentThe position of the patient and the construction of a single-port channel

The patient is placed in the Trendelenburg position. A 2–2.5 cm longitudinal incision is made at the umbilicus layer-by-layer. The port incision protective sleeve is placed into the abdominal cavity and then tightened. The skin and the rectus abdominis are expanded and then connected with the port upper sealing cover, which forms a CO2 pneumoperitoneum.2)The surgeon’s position and instrument layout

Experimental group: the “chopstick technique” group [12]A.The position of the surgeons: The chief surgeon stands at the head of the patient, the camera assistant stands on the patient’s left, and the uterine-lift assistant stands between the patient’s legs.B.The layout of the instruments: The camera and the operator’s two-handed instruments are arranged into a triangle, the camera is located at the top corner of the triangle, and the two operating instruments are located at the bottom corners (Table 1).C.Operation technique: The surgeon’s hands are kept in a straight line with the instruments, and the operation skills are similar to those of traditional laparoscopy. The two instruments have independent fulcrums through the ports, which are not the fulcrums of each other.

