### Measurement and data collection

#### Outcome measures

The following baseline characteristics of patients will be documented: age, BMI, volume of the uterus, concomitant medications, EQ-5D scores, and anesthesiology scores (ASA).

B. The specific process for follow-up (Table 1):

During the screening period (before surgery), surgical indication, inclusion and exclusion indicators, gynecological check results will be investigated.

The collection of data on the day of surgery will include the successful removal of the uterus by the technique as randomized; conversion to laparoscopy or laparotomy; the total operation time (classified as the single-port establishment time, pelvic-abdominal adhesion release time, total hysterectomy time, specimen removal time, and stump suture time); estimated blood loss; intraoperative complications (including blood transfusion, vascular repair, bowel surgery, bladder surgery, ureter operation); and surgeon fatigue.

On the day of discharge, data on hospitalization expenses and the postoperative hospital stay will be collected by the research assessor.

During the 8 weeks after the intervention, postoperative complications (such as a second operation, infection, urogenital tract injury, intra-abdominal hemorrhage, incision hematoma, incision infection) will be recorded and rated by the Clavien–Dindo classification method. Health-related quality of life (EQ-5D) will be assessed again at 8 weeks (Table 2).

**Table 2 Tab2:** Patient’s characteristics and data collection

Timepoint	Study period							
	Enrollment	Allocation	Post-allocation					Close-out
		0	Pre-operation	Operation	Post-operation	Discharge	After 8 weeks	

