### Statistical analysis

The research assistants will send nonblinded data to a statistician for analysis, who will remain blinded to the other investigators until all data analysis is complete. The data will be analyzed with SPSS version 25.0 software. Continuous variables that are normally distributed will be analyzed according to the means and SDs, and discrete variables that are nonnormally distributed will be summarized as medians, ranges, and IQRs. The *T* test and nonparametric analysis will be applied to analyze continuous variables with normal and nonnormal distributions, respectively, and categorical variables will be analyzed by the *χ*
^2^ test or Fisher’s exact test. *P* < 0.05 will indicate a statistically significant difference.

If it is limited to a single missing item, the missing data will be estimated from the given mean values. Imputation will not be attempted if the missing data include the whole table or more than one item. A sensitivity analysis will be performed to determine whether the method used to deal with missing data is appropriate.

According to the analysis of 1534 laparoscopic total hysterectomies by the Netherlands prospective cohort study [17], the surgical time is influenced by the uterine weight and the methods of hysterectomy, and the independent risk factors for surgical conversion are body mass index (BMI), uterine weight, laparoscopic hysterectomy method, and age. The stratified randomization of uterine weight will be conducted. Moreover, the BMI and age subgroups will be evaluated.

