### Main research indicators and the control of confounding factors and bias

The criteria of a newly successful technology are easy to master, preferred by surgeons and ultimately benefiting patients. However, these evaluation indicators are more complicated, with some being subjective, and some are difficult to evaluate. At present, the superior indicator for the evaluation of surgical techniques is operation time, which is also an objective evaluation parameter for differences in surgical techniques. The reduction in operation time can also indirectly reflect the benefits to patients. Therefore, this study selected operation time as the primary endpoint and other indicators, such as the fatigue of surgeons, as secondary indicators.

The size of the uterus affects the difficulty of total hysterectomy, which is the main confounding factor of the influence of the surgical technique on the operation time. According to the size of the uterus, we set up a stratified grouping study to eliminate the influence of uterine size as a confounding factor of the study. The intraoperative separation of adhesions is another influencing factor of surgical difficulty and a major research indicator in LESS hysterectomy. The study excluded cases that may cause severe intraoperative adhesions and added surgical time classifications during the operation: the single-port establishment time, pelvic-abdominal adhesion release time, total hysterectomy time, specimen removal time, and stump suture time, which eliminated research bias.

This study limits the qualifications of surgeons to those who have mastered both technical methods and have completed more than 40 LESS operations, thereby overcoming the learning curve of the new technology. Surgical videos of each operation are retained, and these will be evaluated by the clinical trial data monitoring committee (DMC). Above all, the research results will have better validity and universality.

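### Surgeon fatigue is scored only after the operation and compared without adjustment for surgeon or prior fatigue, which costs precision and leaves it open to surgeon imbalance

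*Protocol article*

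**What the plan says.** - **Role of fatigue.** The Background says the technique will be assessed "by comparing surgical efficacy and surgeon fatigue". Fatigue is the last item under Secondary objectives, and the Discussion on main research indicators groups it with other measures, "such as the fatigue of surgeons, as secondary indicators".
- **Instrument and timing.** Footnote h of Table 2 reads "Fatigue Severity Scale (FSS): score on a 7-point scale". The fatigue row is marked at post-operation and close-out, and the pre-operation cell is empty. The EQ-5D row in the same table does have a pre-operation mark. The baseline list under Outcome measures contains patient characteristics only.
- **Test.** The Statistical analysis section says that the t "test and nonparametric analysis will be applied to analyze continuous variables with normal and nonnormal distributions, respectively". No surgeon term or baseline covariate is mentioned.
- **Surgeons.** Under Interventions: "All the surgeons participating in the study are proficient in the two LESS techniques". The number of surgeons is not given. The Sample size section acknowledges that several surgeons affect operation time and answers this, together with loss to follow-up, by a 15% increase in sample size. The only randomization stratum is uterine size.
- **Blinding.** It covers participants and research assessors. The operating surgeon necessarily knows the technique.

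**The concern.** A single score after the operation combines three things: how tired the surgeon was on arrival, how high or low that surgeon tends to score, and what the operation added. Only the third is of interest. The first two could be measured (a pre-operation score, surgeon identity) and removed, but the stated schedule and test do neither.

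Two consequences follow. Avoidable variation stays in the comparison, so a real difference in fatigue is easier to miss at 34 per arm. In addition, surgeon is not a stratum, and the article does not say whether the surgeon is assigned before or after allocation. The mix of surgeons could therefore differ between arms, and differences in scoring habits would then be read as an effect of technique.

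The score is also subjective and presumably given by the surgeon. The article does not say it is self-rated; this is inferred from the agree/disagree wording of the scale. At stake is one secondary outcome. The primary outcome, operation time, is not affected by how fatigue is scored.

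**Working it through.** **1. The plan's own figure.** The protocol states a sample size for operation time only.
- Difference: 170.1 − 125.72 = 44.38 min. Pooled SD: √((49.97² + 51²)/2) = 50.49 min.
- Two-sided alpha 0.05, power 0.90. The noncentral t gives power 0.898 at 28 per group and 0.908 at 29, so the stated 29 is reproduced.
- 29 × 1.15 = 33.35, rounded up to the stated 34.

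**2. What 34 per arm gives for fatigue.** No fatigue difference or SD is stated. With independent ratings, 34 per arm detects 0.69 SD with 80% power, or 0.80 SD with 90%.

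**3. Adding a pre-operation score.** The pre/post correlation r is not in the document; the range is assumed. Residual variance is multiplied by 1 − r², and the standard error by √(1 − r²). Power is from 4,000 simulated trials per row with a true difference of 0.7 SD.

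| r | 1 − r² | SE factor | SE reduction | Power, post only | Power, adjusted |
|---|---|---|---|---|---|
| 0.3 | 0.91 | 0.95 | 5% | 0.80 | 0.84 |
| 0.5 | 0.75 | 0.87 | 13% | 0.80 | 0.89 |
| 0.7 | 0.51 | 0.71 | 29% | 0.81 | 0.98 |

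The post-only estimate averaged 0.69 to 0.70 against the true 0.7, and type I error was 0.045 to 0.053. Leaving out the pre-operation score therefore causes no bias under randomization, only a loss of precision.

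**4. Surgeon.** Assumed ranges: 2, 4 or 6 surgeons, with 10%, 30% or 50% of rating variance lying between surgeons; 3,000 simulated trials per setting.
- *Surgeon unrelated to allocation.* Type I error of the unadjusted t test is 0.045 to 0.058, so there is no inflation. At a true difference of 0.7 SD, a surgeon term raises power from 0.83–0.86 to 0.91–0.92 at a 30% share, and from 0.84–0.91 to 0.97–0.98 at 50%. At 10% it adds almost nothing (0.81–0.84 to 0.81–0.85).
- *Surgeon mix differs by arm.* If half the surgeons do 60% of one arm and 40% of the other, type I error of the unadjusted test is 0.04 to 0.13. At 70/30 it is 0.07 to 0.36. A surgeon term returns it to 0.04 to 0.06.
- *Technique effect varies between surgeons* (assumed SD 0.3). Type I error is 0.07 to 0.16 unadjusted and 0.09 to 0.20 with a simple surgeon term. The surgeon term does not cure this case.

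The gains in steps 3 and 4 cannot be added together, because a pre-operation score already carries part of each surgeon's scoring level.

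**The case against.** **Randomization already protects the comparison.** A reader might infer that, without a pre-operation score, the trial cannot isolate fatigue caused by the technique. The documents do not support that. Patients are randomized, so the surgeon's fatigue on arrival is balanced in expectation, and step 3 shows an unbiased estimate. This objection stands in full.

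**Repeated ratings by the same surgeons need not inflate error.** All surgeons are proficient in both techniques and can operate in both arms. When surgeon is unrelated to allocation, the t test holds its level. This stands too: bias needs an uneven surgeon mix or a technique effect that varies by surgeon. The article reports neither, but nothing in its randomization prevents the first.

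**Fatigue is secondary, in a trial described as exploratory.** This is correct, and it limits the weight of the point.

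**Covariates may be in an analysis plan that is not shown.** This is fair for the surgeon term, although the article does state a weaker test. It does not apply to the schedule: no analysis plan can recover a pre-operation score that was never collected.

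**A pre-operation score could itself be contaminated.** Table 2 places pre-operation after allocation. A surgeon who already knows the technique could let that colour the score, and adjusting for it could introduce bias. This stands, and it shapes the fix. The article also gives no scale items or recall period, so the size of the pre/post correlation cannot be judged from it.

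**Conclusion.** The point holds as one of precision and of exposure to surgeon imbalance, not of invalidity. The schedule has no pre-operation score, the stated test is unadjusted, several surgeons contribute ratings, and surgeon is not a stratum.

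The size rests on assumptions outside the document. At a pre/post correlation of 0.3 to 0.7 the standard error falls by about 5% to 29%. A surgeon term gains little if surgeons differ by only 10% of the variance and more at 30% to 50%, with partial overlap between the two gains. The bias figures apply only if the surgeon mix differs by arm, which the article neither reports nor rules out.

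The unblinded rater is a separate limit that adjustment cannot remove: a preference for one technique can enter the post-operation score whatever model is used. The primary result is not affected.

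**What to change.** - Have the operating surgeon complete the same scale on the day of surgery, before learning the allocation, and add that time point to Table 2.
- Record surgeon identity for every operation.
- Compare post-operation scores in a linear model with arm, pre-operation score, uterine-size stratum and surgeon. For operations already done without a pre-operation score, adjust for surgeon and stratum only.
- State who rates fatigue, and report it as an exploratory, unblinded rating.

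The cost is one short extra questionnaire per operation and a few model terms, with no change to patients, treatment or sample size. Two limits remain and should be stated with the result: a simple surgeon term does not correct for a technique effect that varies between surgeons, and the pre-operation score does not remove preference bias from the unblinded rater.

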### Data collection and management

The research assessor will record participant data in a case report form (CRF), which will be identified by the number and initial letters of the participants’ names without disclosing their information. Two data managers will independently input and proofread two copies, and establish a limited-access database that conducts computerized editing checks and manual checks.

### Statistical analysis

The research assistants will send nonblinded data to a statistician for analysis, who will remain blinded to the other investigators until all data analysis is complete. The data will be analyzed with SPSS version 25.0 software. Continuous variables that are normally distributed will be analyzed according to the means and SDs, and discrete variables that are nonnormally distributed will be summarized as medians, ranges, and IQRs. The *T* test and nonparametric analysis will be applied to analyze continuous variables with normal and nonnormal distributions, respectively, and categorical variables will be analyzed by the *χ*
^2^ test or Fisher’s exact test. *P* < 0.05 will indicate a statistically significant difference.

If it is limited to a single missing item, the missing data will be estimated from the given mean values. Imputation will not be attempted if the missing data include the whole table or more than one item. A sensitivity analysis will be performed to determine whether the method used to deal with missing data is appropriate.

According to the analysis of 1534 laparoscopic total hysterectomies by the Netherlands prospective cohort study [17], the surgical time is influenced by the uterine weight and the methods of hysterectomy, and the independent risk factors for surgical conversion are body mass index (BMI), uterine weight, laparoscopic hysterectomy method, and age. The stratified randomization of uterine weight will be conducted. Moreover, the BMI and age subgroups will be evaluated.

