## Methods

### Trial design

This single-center study will be a prospective, randomized controlled, double-blind, two-arm, parallel group, exploratory clinical trial carried out at the First Affiliated Hospital of the Third Military Medical University. The participant flow diagram is shown in Fig. 1.

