### Randomization and blinding

In the study, stratified randomization will be adopted. Prior to randomization, all qualified participants will be classified according to uterine size by ultrasonic measurement (class A = uterine size smaller than 10 cm of the maximum diameter, class B = uterine size between 10 and 15 cm of the maximum diameter, and class C = uterine size larger than 15 cm of the maximum diameter), since uterine size is the primary determinant of the operation time for hysterectomy.

The research assistant will acquire a randomized timetable generated by a computer. Trial participants and research assessors will be blinded to the information of group allocation, as ensured by sequentially numbered, opaque and sealed envelopes. The research assistant will be excluded from the results evaluation and data collection. Patients will be blinded to distribution and intervention information. In case of serious adverse events, the outcome evaluator will inform the surgeon to evaluate whether it is related to the intervention and carry out further treatment without unblinding the patient.

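### The trial is labelled double-blind, but nothing shown keeps the assessor blind for the operative records, and the statistician is sent nonblinded data

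*Protocol article*

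**What the plan says.** Trial design describes a "prospective, randomized controlled, double-blind, two-arm, parallel group, exploratory clinical trial". Randomization and blinding says who is meant: "Trial participants and research assessors will be blinded to the information of group allocation", and names opaque, numbered, sealed envelopes as the means of ensuring it.

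Data collection and management then states: "The research assessor will record participant data in a case report form (CRF". It makes no exception for pages about the operation. Under Outcome measures, the day-of-surgery data include "successful removal of the uterus by the technique as randomized; conversion to laparoscopy or laparotomy", together with the operation times, blood loss and surgeon fatigue. Table 2 adds "Conversion to another LESS technique". Interventions places the chief surgeon at the patient's head in the chopstick arm and on the patient's left in the cross arm.

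On the analysis, the Statistical analysis section says: "The research assistants will send nonblinded data to a statistician for analysis". The same sentence calls the statistician blinded in relation to the other investigators, which is not masking to treatment. The section ties the choice between a t test and a nonparametric test to the distribution of the data. Populations for the analyses starts from intention to treat but removes serious protocol violators, giving a single example.

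**The concern.** A reader who sees the double-blind label and the blinded assessor will credit the trial with blinded measurement of its primary outcome, total operation time. The article does not secure that. One role is declared blind and is also given the CRF without division. At least one CRF item can be judged only by someone who knows both the allocated and the performed technique. Envelopes stop foreknowledge before assignment and do nothing for an assessor afterwards. If the person who later grades 8-week complications has handled pages that disclose the arm, that grading is exposed too.

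The second matter is the analysis. When the test follows from the data and exclusions need judgement, seeing the arms first leaves room for choices that move a result near P = 0.05. Both matters can be closed at almost no cost.

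**Working it through.** **1. The blinding statements side by side**

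| Section | What it establishes |
|---|---|
| Trial design | Double-blind, without qualification |
| Randomization and blinding | Patients and research assessors are blind; envelopes are the safeguard |
| Data collection and management | The research assessor records CRF data, no exception stated |
| Outcome measures | One item is success by the allocated technique; no recorder is named for day-of-surgery data, but the research assessor is named for discharge data |
| Table 2 | Switch to the other LESS technique is recorded |
| Interventions | Surgeon's position differs by arm |

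- Whoever judges success by the allocated technique must know the allocation. If that is the assessor, the assessor is not blind. If it is someone else, the article does not say so.
- Anyone timing the operation in theatre can see where the surgeon stands, and so knows the technique in use.
- Nothing stated separates the person recording operative data from the person grading complications after discharge.

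Blinding of the operative records is therefore claimed, but not assured by the arrangements described.

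**2. Sample size, to confirm that it is unaffected**

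Inputs from Sample size calculation: means 170.1 and 125.72 min, SDs 49.97 and 51 min, two-sided α 0.05, power 0.90.

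- Difference: 170.1 − 125.72 = 44.38 min.
- Pooled SD: √((49.97² + 51²)/2) = 50.49 min.
- Normal approximation: n = 2 × (1.960 + 1.282)² × 50.49² / 44.38² = 27.2, so 28 per group.
- Noncentral t: power is 0.898 at 28 and 0.908 at 29, so 29 per group, as stated.
- Expansion: 29 × 1.15 = 33.35, so 34 per group and 68 in all, as stated.

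No blinding assumption enters these figures.

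**3. What arm knowledge at the analysis stage could do**

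The scenarios are assumptions, not document figures: no true difference, 34 per arm, 20,000 runs, normal data or lognormal data with a coefficient of variation of 1/3. The protocol's own values are 49.97/170.1 = 0.29 and 51/125.72 = 0.41, so 1/3 lies between them. The nominal level is 0.05.

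| Analysis rule | Type I error, normal to lognormal |
|---|---|
| Fixed t test | 0.048 to 0.051 |
| Test chosen by a fixed Shapiro-Wilk rule | 0.050 to 0.054 |
| Smaller of the t test and Mann-Whitney P values | 0.057 to 0.064 |
| As above, plus optional removal of the longest operation in the experimental arm | 0.081 to 0.092 |

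The Monte Carlo standard error near 0.05 is √(0.05 × 0.95 / 20,000) = 0.0015. Choosing the test from the data does little harm when the rule is fixed. The rise comes from discretion used with the arms in view, mostly from the optional exclusion.

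**The case against.** The other side has a good deal of force.

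- **Theatre.** No section puts the assessor there. Recording in the CRF fits transcription from theatre notes, and a condensed article may leave the data flow to the full protocol.
- **CRF entries.** A yes/no entry for success by the allocated technique, or for conversion, need not name the arm, and a fatigue score is only a number. A reader might infer that the assessor is certainly unblinded; the documents do not establish that.
- **The statistician.** This role is not on the stated list of blinded roles, and the article openly calls the data nonblinded. A reader might infer a contradiction with the double-blind label; as the article defines its blinded roles, there is none.
- **Analysis choices.** A reader might infer that the statistician settles the test, the exclusions and the missing-data handling with the arms known. The missing-data rule is fixed in the text: a single missing item is filled from mean values, anything larger is not imputed, and a sensitivity analysis follows. No section says who decides exclusions or when. The normality criterion may sit in an analysis plan not shown, and its absence here is no fault.
- **The research assistant.** "The research assistant will be excluded from the results evaluation and data collection" might seem to clash with the assistants sending data to the statistician, but forwarding data is neither collection nor evaluation.
- **Impact.** Total operation time runs on a clock from skin incision, and blood loss comes from the suction device, so an assessor's knowledge has limited room to shift either. The surgeon cannot be blinded under any arrangement.

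All of this stands, and it limits the point. It does not restore the safeguard: envelopes remain the only stated means of keeping the assessor blind, and the label and the CRF assignment remain unqualified. Nor does it give a reason for the statistician to see the arms before the test and exclusions are settled.

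**Conclusion.** The point holds in two parts of different strength.

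The firmer part is that the double-blind label and the blinded assessor are not supported by the recording arrangements described. It rests on reading the assignment of the CRF to the research assessor as covering the day-of-surgery pages, which the text implies but does not spell out. The operative records are affected, including the primary outcome, and the 8-week complication grading may be if the same person does both. The size of any bias cannot be computed from the documents. It should be smaller for total time and suction-measured blood loss than for step times, such as adhesion release, that need a judgement about start and stop.

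The weaker part is that nonblinded data at the analysis stage are an avoidable risk, not a contradiction. A reader might infer from the simulation that the trial's true type I error is 0.08 to 0.09. The documents do not support that: nothing in them permits picking the smaller P value or dropping the longest operation, and a prespecified test and exclusion rule would remove most of the risk.

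The change is worth making because it corrects what readers will believe about the primary outcome. It does not call the randomization, the design or the sample size of 68 into question.

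**What to change.** 1. Replace the unqualified double-blind label with a statement by role and outcome: patients blinded, the assessor of discharge and 8-week outcomes blinded, and the surgeon and recorders of operative data not blinded.
2. Take start, end and step times from the surgical videos already retained for every operation, or from the theatre record where the footage does not cover skin incision or the end of the operation. Footage may itself show the technique, so the gain is a time that can be checked, not a blinded one.
3. Keep the operative CRF pages, including technique and conversion items, from the assessor who grades postoperative complications.
4. Send the statistician the arm coded A/B, and open the code only after the choice of test and the list of exclusions are locked and dated.

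The cost is wording, separation of CRF pages and one recoded variable, plus the loss of a more favourable blinding label. No extra patients are needed and the data handling is minor. Relabelling and arm coding can be done at any time before the analysis, even if recruitment has finished.
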